## 2. Objectives

Utilizing a Hybrid Type I, randomized, stepped-wedge trial at 6 diverse VAMCs as intervention sites and 30 usual care control sites, to implement and evaluate the effectiveness and sustainability of implementation strategies utilized in an Addressing Sleep Apnea Post-stroke (ASAP) program designed to improve facility-level diagnosis and management of OSA. These objectives will be accomplished through the following specific aims:

**Specific Aim 1:** Evaluate the effectiveness of an intervention for the early diagnosis and treatment of OSA among Veterans with ischemic stroke and TIA. The intervention program will include a systems redesign Virtual Collaborative and data monitoring. ASAP includes external facilitation and audit and feedback as implementation strategies, which will be assessed during the intervention period. Sites will locally-tailor and implement an Addressing Sleep Apnea Post-stroke (ASAP) quality improvement program. The sites will choose a diagnostic strategy (i.e., unattended polysomnography [PSG]/home sleep test [HST], in-laboratory PSG, direct to auto-titrating [auto]-PAP) and a therapeutic strategy (e.g., in-laboratory PAP titration, auto-PAP). The primary effectiveness outcome, evaluated at the facility-level, will be the 30-day sleep apnea diagnostic rate. The three secondary effectiveness outcomes will be 1. the 30-day

treatment rate, 2. the 90-day recurrent vascular event rate and 3. the 90-day all-cause readmission rate. We hypothesize that the: mean facility diagnostic rate (PSG within 30 days of presentation) will be 70% for eligible patients during intervention periods vs 7% for controls; the mean facility treatment rate (PAP initiation within 30 days of presentation) will be 50% for intervention vs 2% for controls; mean facility 90-day recurrent vascular event rate (stroke, MI/acute coronary syndrome [ACS], congestive heart failure [CHF] and all-cause mortality) will be 3.5% for intervention vs 10% for controls; and; mean facility 90-day all-cause readmission rate will be 20% for intervention vs 33% for controls. Chart review and administrative data will be used to ascertain outcomes.

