### **3. Study Procedures**

#### **5.1 Study Design**

**5.1.a. ASAP Overview** The ASAP project will be conducted as a Hybrid Type I, randomized, stepped-wedge trial at 6 intervention sites and 30 control sites over a 3.5-year period (Figure 1). The 6 intervention sites will begin the 21-month active implementation period; (orange shading for WAVE 1, green shading for WAVE 2 and yellow shading for WAVE 3) in 3 staggered “steps” with 2 sites per step. Immediately following the active implementation phase for WAVES 1 and 2 will be a sustainability phase up to 7 months in duration (purple shading). WAVE 3 will not have a sustainability phase. This design allows for 3 active implementation data periods of 7-months duration for each WAVE. As seen in Figure 1, there are a variable number of 7-month data periods in the baseline and the sustainability periods by wave. The ASAP quality improvement intervention includes a systems redesign Virtual Collaborative and data monitoring. As part of the quality improvement intervention, sites will locally tailor and implement an ASAP approach, in which each site chooses a diagnostic strategy from a menu that includes unattended PSG, in-laboratory PSG, or direct to auto-PAP approach. Similarly, sites may choose any treatment strategy.

Figure 1. ASAP Project Active Implementation and Sustainability Timeline

[figure not shown]

**5.1.b. Participating Sites** To be eligible for inclusion in ASAP a site had to have >50 stroke/TIA patients per year and have at least 1.0 FTE staff dedicated to systems redesign. The sites were chosen because they are diverse in terms of geography and sleep infrastructure. Data regarding the capacity to perform acute OSA assessment at each site is included in site investigators' letters of support. Furthermore, the sleep clinical champions vary across the sites and include clinicians trained in pulmonary, neurology, and psychiatry; some have on-site sleep laboratories whereas others use unattended PSG or fee-basis for their PSGs.

Table 2 data provide the estimates that were used in the revised power calculations: 111 patients per year will be eligible.

| VAMC (Site)       | Annual Patient Volume (n) a | History of OSA (n) | PSG in prior 5-years (n) | Potentially Eligible (n) b |
|-------------------|----------------------------------------|--------------------|--------------------------|---------------------------------------|

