### **Diagnostic Rate**

(Power for Diagnostic Rate: Active Implementation versus Baseline)

Using a stepped-wedge with 6 VA sites, 8 total time points, 2 sites switching at each step, and approximately 64 patients per site ( $111 \times 7/12$ ) at each step, we should have over 90% power to detect a difference in diagnostic rate of 7% and 15% while varying the coefficient of variation (or intra-cluster correlation). 7% was the observed diagnostic rate in FY2017, and intervention is expected to increase the diagnostic rate to 70% so we are appropriately powered for this primary outcome. The detectable intervention diagnostic rate is provided in the table based on the two-sided test statistic while varying the coefficient of variation. We additionally ran 1,000 simulations with varying treatment effects, including a large random site-effect  $u_j \sim N(0, \tau^2)$ , with  $\tau^2$  based on ICC (.03, .05, .20), a linear time-effect ( $\gamma = 0.005$ ), and assuming a diagnostic rate in the control phase of 7%. We then fit the proposed linear mixed model with time as a categorical variable. Even in the extreme case that our ICC is large (ICC = 0.2), we are still adequately powered to detect the difference in diagnostic rate of 7% and 15% (Table 3). This initial power calculation was revisited to include additional baseline data and a slight reduced sample size because of the COVID-19 pandemic. The results of the updated power calculation did not differ substantively from the initial (above) power calculation.

**Secondary Analyses Effectiveness** The three secondary effectiveness outcomes are 30-day treatment rate, 90-day recurrent vascular event rate and 90-day all-cause readmission rate.

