## **Analysis of the Primary Effectiveness Outcome**

### **Diagnostic Rate Analysis**

A generalized linear mixed model will be fit to the patient-level outcome of diagnostic testing (yes/no) to conduct facility-level inference. The primary effect of interest is the effect of the intervention during active implementation versus baseline. Control sites are included to add accuracy in estimation of the secular time trend. A non-exact match approach is planned for this analysis (i.e., unconditional) since this model is being fit to patient-level data which will be used to conduct facility-level inference and there is no guarantee that patients in control sites that were loosely matched to an intervention site using facility factors are similar. This approach will use all available control site data without pairing specific control sites to each ASAP site. Effects in the model include a site-level indicator of intervention site vs control site, indicator for each site and data period corresponding to active implementation or sustainability phase, and time (as categorical, indicating each 7-month data period). The model will also include a random intercept for site to account for potential correlation among patients from the same site. Our interest is in testing the effect of the ASAP intervention on the proportion of patients who are diagnosed at the site-level. This model will also be fit adjusting for any important patient covariates (i.e., stroke severity). Both unadjusted and adjusted results will be reported. Contrasts from the model will also be estimated. All statistical tests will be two-sided, with p-values < 0.05 considered statistically significant. All analyses will include checking of assumptions and model fit.

**Analysis of Secondary Outcomes** As described above, because the treatment rate can only be assessed among the patients who have been diagnosed, we will be limited in our analysis of treatment. If several patients are diagnosed in the during the control phase (which is unlikely), we would use the same mixed model approach as with other outcomes. However, because we expect to have very

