The business-case analysis will focus on financial costs and savings. We will include all of the ASAP program costs (Table 5) including: staffing and training costs (obtained by staff surveys about time allocations for specific activities which will be converted to staffing costs), equipment costs (obtained by sleep medicine service surveys), and supply costs (obtained by site PI surveys); patient travel reimbursements (if patients are traveling to the VA to obtain sleep services; obtained from VSSC Beneficiary Travel report); and total patient health care costs for inpatient and outpatient utilization (obtained from the VHA Managerial Cost Accounting [MCA] System). We do not expect that the ASAP program will involve changes in space, but if any of the participating sites requires changes in space this will be included in the analysis. We will not include any research-specific costs. The business-case analysis will be built from the VAMC leadership perspective and will therefore not include patient costs. The timeframe for the business-case analysis will be the active implementation phase and no discounting will be performed. If data availability allows, we will compare the business-case analyses across the 6 participating sites. The primary comparison will involve assessing differences between intervention patients versus usual care patients. Veterans Equitable Resource Allocation (VERA) reimbursements will not be considered in the primary business-case analysis because all the patients in the ASAP program have had a stroke or TIA and the intervention is unlikely to influence VERA classification or reimbursements, although we will ask site leadership regarding including VERA in the analysis. The final product of the business-case analysis will be a report and will include the estimated per patient cost for ASAP program implementation and differences in the estimated costs for intervention versus usual care patients. Cost data will only involve data from ASAP sites. As we anticipate that the ASAP program will reduce recurrent vascular events, we hypothesize that the business-case analysis will favor the intervention at sites with the highest baseline recurrent vascular event rate, reducing costs associated with relatively expensive readmissions.

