#### **Specific Aim 4 (Business-Case) Analysis:**

For the business-case analysis, we will evaluate the effect of the intervention on annual patient-level healthcare costs after index admission, while adjusting for annual patient-level healthcare costs prior to admission. To do this, we will include 7-month data periods that occur during baseline and active implementation. Costs will first be converted to the same fiscal year to account for inflation using the Consumer Price Index (CPI). The basic stepped wedge model will be fit using a generalized linear mixed model approach assuming the costs follow a gamma distribution with log link. Model results will be evaluated to check assumptions. The model will include the prior annual healthcare costs as a covariate, time period (as categorical), and active implementation indicator. Additionally, a random site-level intercept will be included to account for any heterogeneity in costs due to unmeasured site-level factors. Some patients may die within 12 months of the index admission and other patients in the last wave of sites may have fewer than 12 months of cost data available due to administrative cutoff of the database. This information will be examined descriptively. Initial models may only use patients with complete cost information available. Alternatively, we will consider treating costs as right censored for those with incomplete information.

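### The patient healthcare-cost model uses the six ASAP sites only, so its effect estimate is imprecise and rests mainly on each wave's first seven active months; control-site costs would help on both counts.

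*Protocol*

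**What the plan says.** Section 5.7.3 (Business-Case Analysis) names the comparison: "The primary comparison will involve assessing differences between intervention patients versus usual care patients". It then restricts the data: "Cost data will only involve data from ASAP sites". No reason is given.

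The Specific Aim 4 analysis paragraph fits a gamma model with log link to annual cost after the index admission. On periods: "we will include 7-month data periods that occur during baseline and active implementation". On terms: "The model will include the prior annual healthcare costs as a covariate, time period (as categorical), and active implementation indicator", plus a random site intercept. There is no site-type term because no control site enters.

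The effectiveness outcomes are handled differently. The Objectives describe six VAMCs "as intervention sites and 30 usual care control sites", and the Diagnostic Rate Analysis explains their role: "Control sites are included to add accuracy in estimation of the secular time trend". The recurrent-event and readmission rates are analysed in a similar way, without the code-red period.

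**The concern.** The protocol expects savings to come through fewer costly readmissions. The readmission effect is estimated with control sites, yet the cost effect expected to follow from it is estimated without them.

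In a stepped wedge with categorical period, a period in which every contributing site is active gives almost no information on the effect unless there is an outside comparator. Once Wave 3 starts, no ASAP site is in baseline. What remains is the contrast in the few periods when the waves differ, and that contrast is dominated by each wave's first active period. The protocol's own Aim 1 sensitivity analysis allows that implementation may take time after kick-off. A cost estimate resting on the first seven months could therefore say little about the established programme, which is what facility leadership would want to know.

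**Working it through.** **Inputs.**
- Size: "Using a stepped-wedge with 6 VA sites, 8 total time points, 2 sites switching at each step, and approximately 64 patients per site" (Power, Diagnostic Rate; 111 × 7/12 = 64.75, taken as 64).
- Active phase: "This design allows for 3 active implementation data periods of 7-months duration for each WAVE" (5.1.a). Wave 3 has no sustainability phase.
- Control sites: 30 (Objectives), or 6 × 4 = 24 under the fallback in the Control Sites section.
- ICC: none is stated for cost. I assume 0.01 to 0.20; the upper end and 0.03 come from the diagnostic-rate simulations.

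**Layout (inferred).** The protocol gives no precision for the cost model, so I checked the machinery and the stagger on Table 3. The method is generalised least squares on site-period means with categorical period, active and sustainability effects, σ² = 0.07 × 0.93, τ = CV × 0.07, n = 64 and power = Φ(δ/SE − 1.96). A six-period layout with steps one period apart and three active periods per wave gives all 12 active-versus-control powers to two decimals (for example 0.77, 0.84, 0.89 and 0.95 at CV 0.3). The protocol says baseline data were added later. Putting two baseline periods in front gives eight periods: Wave 1 active in 4–6, Wave 2 in 5–7, Wave 3 in 6–8. This eight-period version gives powers 1 to 5 points above Table 3, so Table 3 supports the one-period stagger and not the eight-period layout itself.

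**Concurrent comparators.** Active site-periods: 6 sites × 3 = 18. From period 6 no ASAP site is in baseline. Active site-periods there: 6 + 4 + 2 = 12, and 12/18 = 67%. Other staggers, which do not fit Table 3, give 44–56%.

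**Precision.** For site *i* and period *j*, the mean is: period *j* + θ × active + u_i + error (plus a site-type term when controls enter). V_i = (σ²/n)I + τ²J, and Var(θ̂) is the θ element of (Σ X′V⁻¹X)⁻¹. Residual variance is 1 and sustainability periods are removed. This linear model approximates the gamma model.

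| ICC | Var, 6 sites | Var, 6 + 30 | SE ratio |
|---|---|---|---|
| 0.01 | 0.00726 | 0.00173 | √4.20 = 2.05 |
| 0.03 | 0.00754 | 0.00173 | √4.36 = 2.09 |
| 0.20 | 0.00770 | 0.00173 | √4.45 = 2.11 |

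- With 24 controls the ratio is 2.02–2.08.
- With 30 controls, if the last one or two periods drop out for incomplete 12-month costs, it is 1.96–2.01 or 1.76–1.79.
- Other staggers give about 1.7–2.0.
- Deleting periods 6–8 from the six-site model raises its variance by only 4.7–8.2%.

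**What the estimate averages.** θ̂ is linear in the site-period means. If the true effect is θ₁, θ₂, θ₃ in a wave's three active periods, its expectation is a weighted sum with weights adding to 1:
- Six sites: about +0.93 to +0.99, +0.25, and −0.18 to −0.23.
- With 30 controls: 0.35, 0.33, 0.33.

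As an illustration (an assumption, not a forecast), suppose there is no effect in the first seven months and a constant effect D afterwards. The six-site model then expects between (0.25 − 0.18)D = 0.07D and (0.25 − 0.23)D = 0.02D. The model with controls expects about 0.65D.

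**Shifts in the late periods.** A shift in periods 6–8 shared by the ASAP sites moves the six-site estimate by exactly 0. An ASAP-versus-control divergence in those periods moves the control-augmented estimate by about 67% of its size.

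**The case against.** The restriction can be defended as an explicit choice. The control sites are not randomised. They were restricted to the same complexity level and record system and matched on volume and baseline diagnostic rate, not on cost, local wages or COVID-19 burden. Adding them moves weight from the randomised step order to a comparison with loosely matched sites, and the 67% pass-through shows what that could cost. The six-site effect is identifiable, the protocol sets no precision target for cost, and programme costs such as staff time and equipment exist only at ASAP sites. All of this stands. It argues for checks and for keeping the six-site fit, not for going without the extra information: the protocol already accepts a shared trend for its other modelled outcomes.

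Three stronger readings are tempting but unsupported:
- *COVID-19 or the PAP recall biases the planned estimate in the late periods.* Period is categorical, so shifts common to the ASAP sites cancel exactly.
- *The text contradicts itself by comparing with usual care patients while excluding control sites.* The phrase can be read as baseline patients at ASAP sites.
- *The control-site cost data are already in hand.* The Managerial Cost Accounting (MCA) source appears only for the business case, which is limited to ASAP sites. Section 5.6 does not list it among the administrative sources.

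**Conclusion.** The point holds as a worthwhile improvement to an identifiable but weak analysis, not as an error that invalidates Aim 4. Under the inferred layout, two thirds of the active site-periods lack a concurrent baseline site, and the standard error is about twice what it would be with control sites. The planned estimate also mostly reflects the first seven active months and gives the third active period a small negative weight.

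The size rests on the one-period stagger, equal volumes of 64 per site-period at ASAP and control sites, and a linear approximation to the gamma model. The cost ICC is assumed, but the SE ratio hardly changes over 0.01 to 0.20. Under other staggers, or if late patients lack 12-month costs, the gain is smaller (SE ratio about 1.7 to 2.0) but still material. The near-equal weighting with controls applies only when all periods are kept.

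**What to change.** Replace the restricting sentence in section 5.7.3 with wording such as:

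*Programme costs (staff time, equipment, supplies) are collected at ASAP sites only. Healthcare costs for the year before and the year after the index event are extracted from MCA for eligible patients at both ASAP and control sites.*

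In the Aim 4 analysis paragraph, fit the gamma model with site type, categorical period, active indicator, prior-year cost and a site random intercept. Report the six-site fit alongside it as a sensitivity analysis. Check the shared cost trend by comparing ASAP and control sites over the baseline periods, and by comparing the two fits.

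The cost is one further MCA extraction, not now planned, for a control-site cohort already covered by chart review and administrative data, plus the revised wording. The main downside is reliance on a cost trend shared with non-randomised sites: about two thirds of any divergence in the late periods would enter the estimate.

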#### **Specific Aim 4 (Business-Case) Analysis:**

For the business-case analysis, we will evaluate the effect of the intervention on annual patient-level healthcare costs after index admission, while adjusting for annual patient-level healthcare costs prior to admission. To do this, we will include 7-month data periods that occur during baseline and active implementation. Costs will first be converted to the same fiscal year to account for inflation using the Consumer Price Index (CPI). The basic stepped wedge model will be fit using a generalized linear mixed model approach assuming the costs follow a gamma distribution with log link. Model results will be evaluated to check assumptions. The model will include the prior annual healthcare costs as a covariate, time period (as categorical), and active implementation indicator. Additionally, a random site-level intercept will be included to account for any heterogeneity in costs due to unmeasured site-level factors. Some patients may die within 12 months of the index admission and other patients in the last wave of sites may have fewer than 12 months of cost data available due to administrative cutoff of the database. This information will be examined descriptively. Initial models may only use patients with complete cost information available. Alternatively, we will consider treating costs as right censored for those with incomplete information.

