**Data Monitoring** Chart review will be conducted centrally (Indianapolis VAMC/West Haven VAMC) and at the local sites. Chart review will be conducted on all eligible ischemic stroke and TIA patients who are admitted at the participating sites. Patients with ischemic stroke/TIA will be identified using ICD-10 codes in the Corporate Data Warehouse (CDW). The hub will include facility-level data for: OSA diagnosis and ASAP primary and secondary effectiveness outcomes. The hub allows sites to compare their data to other sites and to examine trends over time. Site staff/providers will use these data to iteratively improve ASAP implementation. For example, if sites learn that OSA testing rates are lower after discharge than during the hospitalization period, processes focusing on hospitalized (rather than discharged) patients would be appropriate. To complement data seen on the Hub, the results of the chart review will be provided to implementation sites and will be discussed at the Virtual Collaborative monthly conferences. Furthermore, recognizing that each patient is an opportunity to improve local ASAP processes and procedures, during external facilitation sessions, patient-level data will be reviewed with the sites.

**5.1.d. Implementation Strategy** This project draws explicitly upon the implementation strategies of external facilitation and data and feedback, which will be assessed on an ongoing basis over the intervention period.

**External Facilitation** External facilitation changes over time based on the needs of the team. However, the core elements of relationship-building, methods training, communication, facilitating team-based problem solving, and monitoring performance over time will be preserved through external facilitation from a Lean Six Sigma Black Belt experienced in stroke QI work and ASAP investigators experienced in implementation of post-stroke/TIA OSA programs.

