**5.7.c. Specific Aim 1 (Effectiveness) Analyses** Program effectiveness will be evaluated by a single, primary outcome (diagnostic rate). The diagnostic rate is defined as PSG completion within 30 days of presentation for the index stroke or TIA. **Effectiveness Outcome Ascertainment** We will seek to iteratively improve the CDW algorithms by comparing data to that of the chart review data (e.g., NIHSS data). COVID-19 data has been added to our ASAP administrative data set. COVID-19 data will consist of a combination of: (1) patients with polymerase chain reaction or antigen test results positive for severe acute respiratory syndrome coronavirus 2 (SARS-CoV-2) and; (2) from the VA National Surveillance Tool (NST). Also, pertinent dates related to the impact of the Philips Respironics Recall, indicating VHA-wide availability of PAP, have been added to our data.

Admissions for ischemic stroke and TIA to VAMCs have shown a decline during the COVID-19 pandemic. Furthermore, patients admitted to a VAMC with COVID-19 are not candidates to receive positive airway pressure (PAP) during the index hospitalization.

In considering analyses of the primary outcome, a sensitivity analysis will include re-running the final model with the inclusion of a facility-level, time-varying measure of COVID-19 burden. Although, inclusion of control sites which allows us to adjust for secular time trends may be sufficient to account for the effect of COVID-19 in the model.

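### The Aim 4 cost model plans no version adjusted for the index event, although three Aim 1 models do and the six ASAP sites already hold the data

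*Protocol*

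**What the plan says.** The section Specific Aim 4 (Business-Case) Analysis sets out to estimate the intervention's effect on yearly cost after the index admission "while adjusting for annual patient-level healthcare costs prior to admission". It specifies a "generalized linear mixed model approach assuming the costs follow a gamma distribution with log link". Its fixed effects are listed: "The model will include the prior annual healthcare costs as a covariate, time period (as categorical), and active implementation indicator". In addition, "a random site-level intercept will be included to account for any heterogeneity in costs due to unmeasured site-level factors". No severity or event-type term appears, and no second, adjusted fit is mentioned. The Business-Case Analysis Overview restricts the data: "Cost data will only involve data from ASAP sites".

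Aim 1 is handled differently. Under Diagnostic Rate Analysis, "This model will also be fit adjusting for any important patient covariates (i.e., stroke severity"), and both sets of results are to be reported. The paragraph on the 90-day vascular-event and readmission analyses likewise plans an unadjusted fit and one with patient-level factors.

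On data availability, Data Monitoring (5.1.c) says: "Chart review will be conducted on all eligible ischemic stroke and TIA patients who are admitted at the participating sites". The same paragraph identifies patients by ICD-10 code, and section 5.7.c gives NIHSS as an example of chart-review data. The Missing Data paragraph expects a small amount of missing NIHSS and leaves the choice between complete-case analysis and multiple imputation open.

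**The concern.** Cost in the year after a stroke or TIA plausibly depends on which event it was and how severe it was. Prior-year cost is measured before that event and cannot describe it. The protocol judged severity worth adjusting for in the diagnostic model and patient-level factors worth adjusting for in the two 90-day models, but carried none of this into the cost model. The cost model also lacks the control sites that sharpen the time trend in Aim 1.

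Two things are at stake. Variance that available baseline values could explain stays in the residual and widens the interval for the cost ratio. And if case mix at a site changes between its baseline and active periods, part of that change can be read as a cost effect of the program.

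**Working it through.** The protocol gives no sample size, power, effect size or cost variance for Aim 4, so there is no stated Aim 4 figure to reproduce. The one figure borrowed is the number of patients per site and period, from the power section: 111 × 7/12 = 64.75, which agrees with the stated value of about 64.

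**Precision, simple form.** Let R² be the share of log-cost variance, left after prior cost, that severity and event type explain. The standard error scales by √(1 − R²), and the equivalent gain in patients is 1/(1 − R²).

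| Assumed R² | SE ratio | SE reduction | Equivalent sample |
|---|---|---|---|
| 0.05 | √0.95 = 0.975 | 2.5% | 1/0.95 = 1.05 |
| 0.15 | √0.85 = 0.922 | 7.8% | 1/0.85 = 1.18 |

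**Precision in a stepped-wedge layout.** Figure 1 is not shown, so a layout was assumed: eight periods, two sites per wave, active in periods 4-6, 5-7 and 6-8, with later periods dropped. That gives 2 × (6 + 7 + 8) = 42 site-periods, 18 of them active, and 42 × 64 = 2,688 patients. Generalized least squares on the log-cost scale used categorical period, a site intercept, an assumed residual SD of 1.0 and an ICC of 0.01:

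| Assumed R² | SE of log cost ratio | Ratio detectable with 80% power |
|---|---|---|
| 0 | 0.0852 | 1.270 |
| 0.05 | 0.0831 | 1.262 |
| 0.10 | 0.0810 | 1.255 |
| 0.20 | 0.0766 | 1.239 |

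The detectable ratio is exp[(1.960 + 0.842) × SE]; for the first row, exp(2.802 × 0.0852) = 1.270. With SD 1.5 and ICC 0.05 the SE falls from 0.1309 to 0.1172 at R² = 0.20, which is again about 10%.

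**Bias in the pooled effect.** Assume that the share of strokes shifts by 5 to 10 points and that a stroke costs 1.3 to 2.0 times as much as a TIA. The shift in mean log cost is then d × ln(ratio), from 0.05 × ln 1.3 = 0.0131 to 0.10 × ln 2.0 = 0.0693. Passing this through the same model (ICC 0.03) gives:

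| Where the shift occurs | Bias in the cost ratio |
|---|---|
| All sites, from one calendar period onward | 0% |
| One site, throughout the study | at most 0.3% |
| Active periods of one wave-3 site | 0.1% to 0.7% |
| Active periods of the two wave-1 sites | 0.7% to 3.7% |
| Active periods of all six sites | 1.3% to 7.2% |

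The last row can be checked by hand, because the active indicator takes up the whole shift: exp(0.0131) − 1 = 1.3% and exp(0.0693) − 1 = 7.2%.

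**Size of a chance shift at one site.** In this layout a site has 3 × 64 = 192 active patients and 192 to 320 baseline patients. With an assumed stroke share p of 50-80%, the SE of the phase difference runs from √[0.16 × (1/192 + 1/320)] = 3.7 points to √[0.25 × (2/192)] = 5.1 points. A shift of 5 points at a single site is therefore ordinary sampling noise, which adjustment would partly remove. A shift of that size in the active periods of all six sites would need a cause tied to rollout.

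**The case against.** The strongest objection is that nothing stated is wrong. The protocol calls this the basic model, speaks of initial models, and does not exclude an adjusted version; a statistical analysis plan that is not at hand may contain one. Prior cost is itself a patient-level covariate and the baseline value of the outcome. Wave order is randomized, and the Baseline Characteristics paragraph expects stable case mix and plans summaries by site and time. All of this stands, and it limits the point to an improvement. It does not remove the asymmetry: the protocol writes out the cost model term by term, and where it wants an adjusted companion, as in Aim 1, it says so.

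A reader might infer that the cost effect is already biased, because "Admissions for ischemic stroke and TIA to VAMCs have shown a decline during the COVID-19 pandemic". The documents do not support this. The sentence reports a fall in volume and says nothing about severity or the balance of stroke and TIA. A change common to all sites in calendar time is absorbed by the period effects in any case.

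A reader might also reason that if cost rises by 3-5% per NIHSS point (an assumption), a one-point phase difference at one site moves the result by 3-5%. That would describe the site's own before-after contrast. The specified model estimates one common effect, and a shift confined to one site moves that effect far less.

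Finally, NIHSS is not available for every patient. Entering it with complete-case handling would shrink a model that may already be limited to patients with complete costs. That objection is sound and is met in the fix.

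**Conclusion.** The point holds as a low-cost improvement to a secondary-aim analysis. The stated cost model has no covariate describing the index event and no adjusted companion, unlike three Aim 1 models, although the values are already gathered at the same six sites. The expected gain is an SE about 2.5-8% smaller under an assumed R² of 5-15%, plus protection against within-site case-mix changes that coincide with rollout. Such changes could move the pooled cost ratio by anything from a fraction of a percent to about 7% under the assumed shifts and cost ratios. The documents neither show such a change nor give cost inputs, so the size is illustrative: it rests on the assumed R², SD, ICC, cost ratios and period layout.

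**What to change.** In Specific Aim 4 (Business-Case) Analysis, prespecify an adjusted gamma model with log link that keeps the existing terms and adds index event type (stroke or TIA), NIHSS and age. Report it beside the basic model, as the protocol already does for the Aim 1 outcomes. State that missing NIHSS will be multiply imputed, so that adjustment drops no further patients. Name the covariates here explicitly, because the Aim 1 text names only stroke severity and fixes no missing-data rule that could be carried over.

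The cost is one additional model and a small amount of imputation. No new data collection is needed: NIHSS comes from chart review, event type from the ICD-10 codes, and age from the demographics that chart review already covers.
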